## Data collection

### Baseline

#### Control

Paper-CCM was used to assess and treat children for between 2 and 7 weeks (dependent on clusters’ assigned sequence from randomization), as per standard practice. Facilitated by the Sick Child Form, patient data routinely collected by HSAs through a series of questions and physical examinations was recorded in the village clinic register and included: demographic data (i.e., child and caregiver name, child date of birth, relationship of caregiver to child, physical address); the presence and duration of “sick” signs (i.e., diarrhea for less than 14 days without blood in stool, fever for less than 7 days, red eye for less than 4 days, fast breathing) and “danger” signs (i.e., cough for 21 days or more, diarrhea for 14 days or more, blood in stool, fever lasting for 7 days, convulsions, not able to feed or drink anything, vomits everything, red eye for 4 days or more, red eye with visual problem, chest recession, very sleepy or unconscious, palmar pallor, red/yellow on MUAC tape, swelling of both feet); treatment decision (i.e., urgent referral or treat at home and advise on homecare, including when to return for follow-up) and medication dispensed (e.g., antibiotics, oral rehydration therapy).

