#### Intervention

After HSAs in each cluster completed their allocated time in the control and the second training workshop, they transitioned to using the SL eCCM App in addition to paper-based CCM for between 2 and 7 weeks. The same patient data recorded in the control was collected and recorded concurrently in the SL eCCM App and village clinic register. Dual-use and double-data entry were necessary due to functional limitations of the SL eCCM App and because completion of the village clinic register is mandatory for monthly aggregation of cases for country-level disease surveillance purposes. During technical malfunctions (e.g., software bugs, power failures, etc.) that prevented use of the App, or scenarios where caregivers could not be consented, HSAs temporarily reverted to paper-CCM only. HSAs dispensed treatment using recommendations prompted by the SL eCCM App, but could elect to follow recommendations of paper-CCM where they strongly disagreed with the App’s recommendations. Use of the breath count feature to measure RR was encouraged, but HSAs could choose to use the stopwatch (as per standard practice) if they preferred.

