### Sample size

We planned to recruit a total of 102 HSAs. Our sample size estimation is based on change in proportions of the primary outcomes expected pre and post intervention. Assuming an alpha of 0.05, 97 HSAs would provide 80% power for a minimum detectable rate of change between 6 and 7% in referral, re-consultation and hospitalizations (one-sided test). We assumed a 1% urgent referral rate, based on the proportion of children identified as needing to be urgently referred at clinics in a previous study conducted in Malawi [11]. As an urgent referral rate of 8% has been estimated as a reasonable consensus referral rate at clinics in sub-Saharan Africa [43, 44] that are correctly adhering to IMCI, we assumed the addition of the SL eCCM App could improve urgent referral rates close to this estimate; a 6–7% change between the control and intervention was, therefore, a conservative estimate of this assumption. Given the short trial duration and potential of perceived elevated status through smartphone ownership in this setting [45], we did not expect many HSAs to drop out. We believed that recruiting 102 HSAs would be sufficient to accommodate potential dropout, to ensure we achieved our desired sample size. Power calculations were computed using the “Power and Sample Size” option in Stata v. 13 (StataCorp, College Station, TX, USA) [46] which is appropriate for rates, specifically “*longitudinal studies, where the same cases serve as their own controls over time*” [47].

A total of 300 parents/caregivers whose children were referred to a higher-level facility or re-consulted at a village clinic completed the PCQ. It was estimated that approximately 600 children would be eligible for referral to a health care facility assuming: a 1% referral rate among 4000 children in the control group (*n* = 40), a 7–8% referral rate (change 6–7% from the initial 1% referral rate) among the same number of children in the intervention group (*n* = 300) and a 6–7% under-referral rate in the control group (*n* = 260). Considering the challenges in identifying those who were referred but did not present at a health care facility, or those who were not referred but did visit a health care facility or represented at a village clinic, and the possible withdrawal or loss to follow-up of parents/caregivers, it is estimated that at least half (*n* = 300) of the eligible cases will be followed up as part of the cost evaluation.

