#### Statistical/analysis methods

Primary outcome data will be evaluated using pairwise comparisons during the control and intervention periods. Analyses will be conducted at the level of the HSA, taking into consideration the number of index visits that occurred during each period, and will include descriptive statistics relating to each outcome (i.e., referral, re-consultation and hospitalization rates); tests of differences by control/intervention period, and multivariate modeling to allow for adjustment of potential confounding factors within each period. Bivariate descriptive statistics will present proportions for categorical variables or means/standard deviations for continuous and categorical data (respectively), for control/intervention periods. Measures of change will be calculated and two-proportion z-tests or chi-square tests will be used to measure unadjusted differences (depending on test assumptions met). We will conduct multivariate analysis using linear regression to evaluate change in outcomes adjusted for composition of children at each HSA by age, gender, symptoms, location (urban/rural) and proximity to the nearest higher-level health facility. For these models, assumptions will be tested, transformations of variables will be made if needed, and a-priori confounders will be evaluated for inclusion in models. Effect modification will be tested by interactions with age and gender. A secondary analysis will be done at the level of the child adjusting for HSA as a cluster variable. Potential confounders and effect modifiers will also be tested in these models. Data analysis and reporting will be conducted with Consolidated Standards of Reporting Trials (CONSORT) [51].

A cost-consequence analysis will be conducted to report the costs and consequences under the control and intervention. All costs of seeking and receiving care for the control and intervention groups will be calculated separately in a disaggregated way at the household level. Direct costs (e.g., out-of-pocket payments and transportation costs), indirect costs (e.g., costs of parent/caregiver productivity loss) and consequences (e.g., hospitalization days) collected through the PCQ will be compared between parents/caregivers enrolled in the control and intervention phases.

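### The unadjusted z or chi-square test treats control and intervention visits as independent samples, so area differences leak into it and inflate its type I error

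*Protocol article*

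**What the plan says.** All references are to the protocol article.

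Under Statistical/analysis methods, the comparison is described in four steps:

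- The form of the primary comparison: "Primary outcome data will be evaluated using pairwise comparisons during the control and intervention periods".
- The level: "Analyses will be conducted at the level of the HSA, taking into consideration the number of index visits that occurred during each period".
- The unadjusted tests: "two-proportion z-tests or chi-square tests will be used to measure unadjusted differences (depending on test assumptions met".
- The adjusted and secondary analyses: "We will conduct multivariate analysis using linear regression to evaluate change in outcomes adjusted for composition of children at each HSA", then "A secondary analysis will be done at the level of the child adjusting for HSA as a cluster variable".

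Under Sample size, the power routine is justified as suited to "longitudinal studies, where the same cases serve as their own controls over time".

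On time in each phase, the Control section says "Paper-CCM was used to assess and treat children for between 2 and 7 weeks (dependent on clusters’ assigned sequence from randomization", and the Intervention section says of the HSAs that "they transitioned to using the SL eCCM App in addition to paper-based CCM for between 2 and 7 weeks". Trial design and Randomization, allocation and blinding add that there are six clusters formed by geography, assigned to crossover timing by simple randomization.

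**The concern.** A two-proportion z-test, or its chi-square equivalent, asks whether two independent groups share one event rate. It has no term for the HSA, the area or the pairing of an HSA with itself. The design sections describe something different: every HSA appears in both phases, and the power statement relies on that.

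The mismatch matters because the wedge is unbalanced within cluster. A cluster that crosses over early gives few control visits and many intervention visits; a late one does the reverse. If areas differ in referral, re-consultation or hospitalization rates, the two phases differ even with no App effect and flat calendar time. A clustered standard error would widen the interval but would not move the point estimate. The plan itself expects place to matter: it lists urban/rural location and proximity to a facility as adjustment variables, and Data management says location may affect the quality of patient records.

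At stake is the p-value attached to each unadjusted difference.

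**Working it through.** **The plan's own figure.** The Sample size section gives 97 HSAs for 80% power, one-sided alpha 0.05, and a change of 6 to 7 points from 1%. A paired calculation with all discordance in one direction, n = (1.645√d + 0.842√(d − d²))²/d², gives 100.9 at d = 0.06 and 93.0 at d = 0.065. So 97 HSAs detect about 6.2 points, inside the stated range. A two-sample arcsine formula gives 6.6 points, also inside it. The figure therefore does not show which formula was used; the stated rationale is what points to pairing.

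**Cluster mix by phase.** Assume one-week steps and nine weeks per cluster: control weeks 2, 3, 4, 5, 6, 7 and intervention weeks 7, 6, 5, 4, 3, 2 in crossover order. Each phase has 27 cluster-weeks. With 17 HSAs per cluster and 8000/(102 × 9) = 8.71 children per HSA-week, that is 27 × 17 × 8.71 ≈ 4,000 children per phase, matching the Sample size section. The first cluster supplies 2/27 = 7.4% of control and 7/27 = 25.9% of intervention visits; the last supplies the reverse.

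**Spurious difference with no App effect and no trend.** Intervention minus control = Σ(intervention weeks − control weeks) × p_k / 27, with weights 5, 3, 1, −1, −3, −5 (sum of squares 70).

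Extreme illustration: assumed area rates of 5, 7, 9, 11, 13, 15% in crossover order.
- Control: 305/27 = 11.3%. Intervention: 235/27 = 8.7%. Difference −70/27 = −2.6 points.
- Standard error with 4,000 per phase: √(2 × 0.10 × 0.90/4000) = 0.67 points, so |z| = 3.9.

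Over all 720 orderings of those rates the mean difference is 0 and its SD is √(70 × 14)/27 = 1.16 points, where 14 is the variance of the six rates (70/5). Only 2 of the 720 orderings give a shift as large as 2.6.

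**Type I error.** The spurious SD from clusters is √70 × CV × p/27. HSA-level variation within clusters, assumed CV 0.5, adds √(70/17) × 0.5p/27. The nominal two-sided 5% pooled test then rejects with probability about 2Φ(−1.96 × SE/total SD), where total SD² = SE² + cluster SD² + HSA SD²:

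| Event rate | Cluster CV | SE (points) | Cluster SD | HSA SD | Approximate rejection | Two simulations |
|---|---|---|---|---|---|---|
| 1% | 0.25 | 0.22 | 0.08 | 0.04 | 7% | 7%, 6% |
| 1% | 0.5 | 0.22 | 0.15 | 0.04 | 11% | 12%, 12% |
| 4% | 0.25 | 0.44 | 0.31 | 0.15 | 12% | 14%, 13% |
| 4% | 0.5 | 0.44 | 0.62 | 0.15 | 27% | 28%, 29% |
| 10% | 0.25 | 0.67 | 0.77 | 0.38 | 23% | 23%, 24% |
| 10% | 0.5 | 0.67 | 1.55 | 0.38 | 45% | 45%, 47% |

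Within-HSA tests (paired, or HSA-stratified Mantel-Haenszel) stayed at about 4 to 6% in the same simulations, none of which had a calendar trend.

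**Exposure to calendar trend.** On the same grid, numbering calendar weeks 1 to 9, pooled control visits have mean week 83/27 = 3.07 and pooled intervention visits 187/27 = 6.93, a gap of 3.85 weeks. Within any one HSA the gap is 9/2 = 4.5 weeks. A within-HSA comparison without a period term is thus 4.5/3.85 = 1.17 times as exposed to a linear trend as the pooled test.

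**The case against.** The strongest reply is that the protocol never says children are pooled. It says pairwise and HSA-level, and testing each HSA's control visits against its own intervention visits would fit those words and cancel area mix. That is fair as to wording. But the outcomes are yes/no per index visit, so pooled counts by phase are the natural input to a two-proportion test. If a paired analysis was meant, the named test is still the wrong one.

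Second, the same section goes on to an HSA-level regression on change, adjusted for location and proximity, and a child-level model adjusting for HSA. This stands: the first, and the second if HSA enters as a term, largely remove stable area differences. Nothing in the article makes the unadjusted test the basis of the trial's conclusion.

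Third, a reader might infer a systematic bias for or against the App, or take the 2.6-point shift as typical. The documents support neither. Sequence is randomized, the spurious difference averages zero, and 2.6 points is the extreme ordering.

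Fourth, the effect is small for urgent referral. At the assumed 1% control rate and cluster CV 0.5 the spurious SD is 0.15 points, about one fortieth of the planned 6 to 7 point change. The larger rejection rates need event rates that the article does not state.

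Fifth, moving within HSA without a period term increases exposure to calendar trend. That is correct and shapes the fix.

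**Conclusion.** The test named for the unadjusted difference does not match the comparison the protocol describes. With few clusters and mirror-image phase mixes, it picks up stable area differences by chance of the draw and rejects too often: about 6 to 12% at a 1% event rate and 23 to 47% at 10%, against a nominal two-sided 5%.

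These sizes rest on assumptions: one-week steps, equal recruitment per HSA-week, visits pooled by phase, cluster CV 0.25 to 0.5, HSA CV 0.5, and no calendar trend. The article gives no between-area variation; if areas share one rate and HSAs do not vary, the test holds its level.

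The defect is confined to the unadjusted test. It would go too far to conclude that the adjusted results are invalid or that the referral effect the trial was sized for could be an artefact of area mix. The sentence should still be corrected, because the article fixes the test by name and it contradicts its own design statements.

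**What to change.** In Statistical/analysis methods, replace the two-proportion z or chi-square tests with a within-HSA comparison that also includes calendar period. Examples are an HSA-stratified risk difference or a visit-weighted paired HSA difference, each extended with period terms. Show pooled phase percentages as description only, without a p-value.

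The change is one sentence and needs no new data. The price is precision, on the same assumed grid and taking visits as independent with a common variance:

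- HSA stratification alone: information Σ(control × intervention weeks)/9 = 104/9 = 11.56, against 27 × 27/54 = 13.5 pooled. Standard error ratio √(13.5/11.56) = 1.08, about 8% larger.
- Adding week indicators: the between-week sum of squares of the treatment indicator is 6 × 1.278 = 7.67, leaving 11.56 − 7.67 = 3.89. Ratio √(13.5/3.89) = 1.86.

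The second cost is substantial, but it is what separating the App from calendar time requires in this design. At a 1% rate it takes the standard error from 0.22 to about 0.41 points, still small against a 6 to 7 point change. At 10% it goes from 0.67 to about 1.25 points.

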Correct identification of children requiring urgent referral is largely dependent upon CHWs’ fidelity to CCM guidelines, which has been frequently reported as suboptimal [3, 7–10]. Poor completion of relevant CCM assessment items may hinder early recognition of serious illness, reducing urgent referrals to higher-level facilities. Information about CCM-directed urgent referral rates in Malawi is limited. However, assessment of the quality of implementation of the CCM program after national scale-up in 2008 reported that CHWs on average made two urgent referrals (per 1000 children) each month [11]. Given the countries’ annual childhood mortality rates from pneumonia (23%), malaria (14%) and diarrhea (18%) [12], this suggests that many children meeting the classification for urgent referral are not being identified. Under-referral risks repeat consultations [13] for the same illness episode as well as hospitalization of those children with serious illness who are left untreated. But, due to the lack of an integrated and electronic medical record system [14, 15], it is unclear which children are brought back to village clinics because they are still unwell, and which of those admitted to hospital were urgently referred by CHWs at the index visit.

Of equal importance is that children who are urgently referred are actually taken to higher-level facilities (in other words, that the referral is completed) when advised [16, 17]. Failure to follow recommendations risks the development of chronic conditions or acute complications [18]. It is suggested that over 50% of caregivers in sub-Saharan Africa whose children are urgently referred, do not take their child for onward care [16, 19–21]. Prohibitive financial and time-related costs incurred by caregivers travelling large geographical distances to facilities [22], and mistrust in CHW “diagnoses” and treatment decisions [23, 24] have been cited as factors contributing to poor referral completion rates.

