Utilizing mobile health (mHealth) technologies (e.g., smartphones, tablets) to deliver CCM could encourage the dispensation of more appropriate treatment recommendations [25] thereby increasing urgent referral rates. Potential improvements may be underpinned by a combination of better control of how the end-user navigates through assessment questions (e.g., built-in validation rules forcing completion of relevant fields with valid data before advancing to the next field/screen) [26]; enhanced CHW motivation linked to the prestige of using advanced technology in a predominantly paper-based health care system; automated presentation of the next-steps reducing reliance on memory [27], and heightened perceived efficacy and caregiver trust in CHWs’ decisions linked to clearer explanations about the child’s condition and recommended treatment [27].

Despite the opportunities that mHealth may afford for circumventing some of the limitations of current paper-based delivery [26], there is a paucity of evidence demonstrating the comparative benefits of deploying digitized versions of CCM on health service utilization and associated patient costs. To address this evidence gap in a pragmatic cluster-randomized trial, we will evaluate the added value of an electronic CCM App (truncated to SL eCCM App) developed as part of the Supporting Low-cost Interventions For disEase control (Supporting LIFE) program. As well as contributing to the broader mHealth literature, we anticipate that trial findings will provide Malawi’s mHealth Working Group with empirical data, which can be used to inform policy regarding the opportunities to Malawi of introducing such interventions for CCM. Our hypothesis is that adding the SL eCCM App to sick child assessments will increase urgent referral rates and reduce re-consultation and hospitalization rates.

The main objectives of this trial were to determine the:▪ Added value of the SL eCCM App (used with paper-CCM) on referral, re-consultations and hospitalization rates among acutely unwell children aged under 5 years, compared with paper-CCM alone▪ Factors influencing caregivers’ decisions to comply with urgent referral recommendations▪ Direct and indirect costs to caregivers presenting to higher-level facilities and/or re-attending village clinics after the index visit when using paper-CCM and the paper-CCM + SL eCCM App

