### The Supporting LIFE electronic Community Case Management Application

SL eCCM App is a smartphone App developed for Android OS 3.0 Honeycomb or above; the smartphone selected to run the App for this trial was the HTC Desire 526G. The App is in English and replicates the paper-based CCM decision aid (i.e., the Sick Child Form) in terms of wording and order of presentation of assessment questions (Fig. 4). Patient data is entered via a touch-sensitive dynamic interface. Field validation forced HSAs to complete all required fields prompted by the App’s decision rule and within clinically valid parameters. Current configuration of the SL eCCM App only permits data entry and so previously entered records cannot be retrieved. Included in the App is a countdown tap-screen feature for measuring RR. The number of screen taps within 60 s equates to a child’s RR. Whilst 60 s was the default measurement period for the trial, the App permits the user to select shorter periods (i.e., 15, 30 and 45 s), where a RR equivalent of 60 s is calculated from the time intervals between taps. HSAs were encouraged to use this feature, but could elect to use the stopwatch (as per standard practice). The SL eCCM App uses RESTful web services communicating over JSON to a Cloud-based web server, running on an Amazon Elastic Compute Tomcat instance. The web-server comprises a middle-tier Spring Model-View Controller framework and uses Java Persistence API to communicate to a back-end MySQL database running on an Amazon Relation Database Service instance. My SQL database (referred to as the SL central database) is supported by Amazon Web Services (AWS) Cloud data storage solutions, and has been created to store uploaded patient data from the SL eCCM App (Fig. 5). Patient data is uploaded onto the SL central database when the App is physically synced with the central database. The robustness and fidelity of the App’s clinical algorithm to paper-CCM was tested iteratively over the 4 years of development against a suite of automated tests. It also underwent additional manual checks by members of the study team (which includes a family physician), by creating artificial clinical scenarios and cross-referencing the logic with the Sick Child Form), as well as with 12 HSAs in a feasibility study conducted in Malawi between July and September 2015 [15].

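### The adjusted model conditions on HSA-recorded symptoms, which the App is meant to change, so it can remove part or all of the App's effect from the adjusted estimate

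*Protocol article*

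**What the plan says.** The protocol article's Statistical/analysis methods section plans two layers for the primary outcomes. The first is a set of unadjusted comparisons of control and intervention periods, by z- or chi-square tests. The second is a linear regression of change in outcomes at HSA level, "adjusted for composition of children at each HSA by age, gender, symptoms, location (urban/rural) and proximity to the nearest higher-level health facility". On covariate choice it adds that "a-priori confounders will be evaluated for inclusion in models". A secondary child-level analysis will test potential confounders in the same way.

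The Data collection section shows where symptom data come from. In the control phase, "patient data routinely collected by HSAs through a series of questions and physical examinations was recorded in the village clinic register". In the intervention phase: "The same patient data recorded in the control was collected and recorded concurrently in the SL eCCM App and village clinic register". The section on randomization, allocation and blinding states that neither participants nor the trial team were blinded.

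The Background gives the causal argument: "Poor completion of relevant CCM assessment items may hinder early recognition of serious illness, reducing urgent referrals to higher-level facilities". It then lists ways the App might raise referral. One is "built-in validation rules forcing completion of relevant fields with valid data before advancing to the next field/screen", and another is "automated presentation of the next-steps reducing reliance on memory". HSA motivation and caregiver trust are also named. The section describing the App confirms the first feature as built: "Field validation forced HSAs to complete all required fields".

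**The concern.** A covariate used to control confounding should not itself be changed by the intervention. Here the symptom composition of an HSA's children is measured after the phase is set, by the person whose behaviour the App is meant to alter, and with the App in hand in one phase only. If the App leads HSAs to find and record signs they would otherwise have missed, recorded symptoms rise because of the App and referrals rise because of the recorded symptoms. Holding recorded symptoms fixed then removes that part of the benefit.

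What is at stake is how the adjusted result is read. It is presented as the analysis that deals with confounding. If it is null while the unadjusted difference is positive, the natural reading is that intervention-phase children were simply sicker. The same pattern would appear if the App had worked through better detection, and the model cannot tell the two apart.

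**Working it through.** No stated figure is in dispute, so the check has two parts: the causal order in the text, and an illustration of size.

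**Causal order**

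1. The only index-visit symptom data described are the sick and danger signs the HSA elicits and records (Control and Intervention subsections). The Follow-up section collects index-visit treatment decisions and later attendances. It describes no independent measure of symptoms at the index visit.
2. The Background says incomplete assessment hides serious illness and lowers referral. The Background and the App section say forced field completion is meant to correct this.
3. The order is therefore App, then more complete recording, then referral. Recorded symptoms are the middle link.
4. Automated next steps act after signs are recorded, so that part of any effect survives the adjustment.

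**Size**

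Inputs from the protocol: 102 HSAs and 8000 children, so 8000/102/2 ≈ 39 children per HSA per period; a 1% control referral rate; a planned change of 6–7 points. Assumed inputs: a true danger-sign prevalence averaging 8%, and the recording and referral probabilities below. The 1% and 8% in the Sample size section are referral rates. The protocol gives no sign prevalence or recording rate.

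Referral rate in a phase = prevalence × P(sign recorded) × P(referred, given recorded). The HSA-period referral rate was regressed on period, with and without the recorded-sign rate (400 simulated trials per scenario).

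| Assumed pathway | P(recorded), paper → App | P(referred), paper → App | Referral rate, paper → App | Unadjusted | Symptom-adjusted | Lost |
|---|---|---|---|---|---|---|
| Recording only | 0.125 → 0.94 | 1 → 1 | 1.00% → 7.52% | 6.5 | 0.0 | 100% |
| Recording only, 90% referred | 0.14 → 1.00 | 0.90 → 0.90 | 1.01% → 7.20% | 6.2 | 0.0 | 100% |
| Recording and decision | 0.35 → 1.00 | 0.36 → 0.94 | 1.01% → 7.52% | 6.5 | 2.3 | 64% |
| Decision only | 0.95 → 0.95 | 0.13 → 0.99 | 0.99% → 7.52% | 6.5 | 6.5 | 0% |

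In least squares, adjusted effect = unadjusted effect − b × (difference in recorded-sign rate), where b is the slope of referral on recorded signs.

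- Recording only: the recorded rate differs by 8 × (0.94 − 0.125) = 6.52 points and b = 1, so 6.52 − 6.52 = 0.
- Recording and decision: the recorded rate differs by 8 × (1.00 − 0.35) = 5.2 points. The simulated values before rounding are 6.49 and 2.33, so b = (6.49 − 2.33)/5.2 = 0.80 and the loss is 4.16/6.49 = 64%.
- Decision only: the recorded rate does not differ, so nothing is removed.

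A separate simulation used the change-score form of the model, regressing each HSA's change in referral on its change in recorded signs. It assumed signs recorded in 1% of children on paper and 7% with the App, with 90% of those referred in both phases. The expected effect is 0.9 × (7 − 1) = 5.4 points. The simulation gave 5.43 unadjusted and −0.03 adjusted. It also assumes that the whole effect runs through recording, and it used 90 children per HSA, somewhat more than 8000/102 ≈ 78.

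**The case against.** Several counter-arguments have force.

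- **The loss depends on the pathway.** A reader might infer that the adjusted model erases the App's effect. The documents do not support that. The zero results follow from assuming that every extra referral comes through a newly recorded sign, whereas the Background also names automated next steps, motivation and trust. This limits the size of the loss but does not make recorded symptoms a valid confounder.
- **Unadjusted comparisons are planned.** A reader might also infer that the primary result as a whole is compromised. It is not: the protocol does not name the regression as the sole primary result, and a gap between the two estimates would be visible. The problem is that the gap could be misread.
- **Symptoms need not mean danger signs.** The term could be limited to presenting complaints, which would block less. The text sets no such limit. Fast breathing, classed as a sick sign, may also be measured differently by phase because the App supplies its own breath counter.
- **Covariates are still to be evaluated, and a full analysis plan is promised.** Symptoms are nonetheless named outright, and the rule does not restrict candidates to variables the App cannot affect. Evaluation on the data would tend to keep recorded signs if they track both phase and referral, as they would if the App works through detection.
- **Case mix can differ between phases.** This is a legitimate reason to want symptom adjustment, and it stands. HSA-recorded signs, however, cannot separate sicker children from better detection.

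A further inference would be that re-consultation and hospitalization would look artificially favourable after adjustment. Neither the protocol nor the calculations above cover those outcomes, so no such claim is made.

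**Conclusion.** The point holds for the adjusted estimates. The protocol lists as a confounder a variable that, by its own account, the intervention should change on the way to the primary outcome. The adjusted HSA-level estimate loses the share of the effect that runs through sign detection, and the child-level estimate is open to the same loss if symptoms enter there. That share lies anywhere from none to all: 6.5, 2.3 or 0.0 points left of about 6.5 in the illustrations. These figures rest on an assumed sign prevalence and assumed pathway splits, and on the symptom term including signs recorded by the HSA. They show a range and do not predict the trial's result.

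**What to change.** Restrict the main adjusted HSA-level model and the child-level secondary model to variables the App cannot affect: child age, gender, location and proximity to a higher-level facility. Add calendar time where the data structure allows, for example with HSA-by-period or child-level records. A single change score per HSA, pooled over several weeks in each phase, cannot simply take a calendar-week term. State that candidate confounders must not be open to influence by the App. Report any model containing HSA-recorded sick or danger signs only as a labelled sensitivity or mechanism analysis, and say which signs enter it.

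No new data are needed. The costs are a change of analysis wording, some restructuring of the data if calendar time is added, and less control of true case-mix change in the main adjusted model. Calendar time covers that last item only in part, since case mix may also shift within individual clusters. The sensitivity analysis can probe the remainder.
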